### Measurements

Urine will be collected and monitored carefully at 6 h after randomization, and the cumulative urine output will be calculated every 24 h. Vital signs and symptom improvement assessed using a 7-point Likert scale will be recorded upon admission, and 24 and 48 h after randomization. Similarly, serum sodium, potassium, and chloride will be evaluated at admission and after 12, 24, and 48 h, respectively, while urinary creatinine and sodium will be sampled at randomization and after 6 h. After randomization, serum urea and creatinine will be re-assessed at 24 and 48 h. In addition, aspartate aminotransferase (AST), alanine aminotransferase (ALT), and N-terminal pro B-type natriuretic peptide (NT-proBNP) were evaluated upon admission and at the end of the study. A summary of the study assessment time frame is presented in Appendix 1. Senior cardiologists will perform echocardiography upon admission, and at 24 and 48 h afterward, according to the echocardiography protocol described in Appendix 2.

### Endpoints

The primary endpoint was the cumulative urine output at 48 h after randomization. The secondary endpoints include the improvement of fractional excretion of sodium at 6 h, total dose of furosemide, changes in the body weight, net fluid loss, improvement of dyspnea by the 7-point Likert scale, reduction of diastolic dysfunction parameters on echocardiography, incidence of clinically relevant WRF, and changes of NT-proBNP at 48 h. Clinically relevant WRF is defined as an increase in serum creatinine level ≥0.3 mg/dl within 48 h accompanied by the doubling of furosemide dose according to the diuretic treatment protocol. A summary of the study endpoints is shown in Appendix 3.

Safety will be assessed based on the adverse effects reported throughout the study with vital signs, physical examination, clinical laboratory tests, and 12 lead-electrocardiogram. Safety topics of special interest include severe hypernatremia (plasma sodium increase > 12 mEq/24 h), hypokalemia, and hepatic injury (elevation of AST and/or ALT > three-fold the upper limit of the normal). Adverse effects and laboratory abnormalities were compared between the two treatment groups.

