**Methods and Results:**

This single-centered, open-labeled, randomized, and controlled trial enrolled 128 patients hospitalized with AHF, as participants. These patients with a wet-warm phenotype, whose estimated glomerular filtration rates are of ≥15 ml/min/1.73 m^2^ and ≤ 60 ml/min/1.73 m^2^, with a cumulative urine output of <300 ml 2 h after the first dose of intravenous furosemide, will be randomly assigned 1:1 to receive standard care with an uptitrating intravenous furosemide alone, or a combination therapy with 15 mg of tolvaptan administered once daily for 2 days. The standard furosemide treatment will follow the latest position statements of the Heart Failure Association. The primary endpoint is the cumulative urine output at 48 h. The key secondary endpoints include the improvement of fractional excretion of sodium at 6 h, the total dose of furosemide, and the incidence of worsening renal function (WRF) at 48 h.

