### Study Flow and Loop Diuretic Strategy

On admission, patients with AHF with wet-warm phenotype will be given a starting dose of intravenous furosemide that is one to two times the 24-h oral furosemide dose prescribed before the admission home dose or 20–40 mg for treatment-naive patients with loop diuretic. Patients will be asked to immediately empty their urinary bladder before the first dose of intravenous furosemide. If eligible for inclusion in the study, at 2 h after the first intravenous furosemide, they will be randomly assigned 1:1 to receive a standard care with intravenous furosemide alone or a combination therapy with 15 mg of tolvaptan, once daily for 2 days. In both groups, the loop diuretic strategy strictly follows the modified 2019 position statement from the Heart Failure Association of the European Society of Cardiology (ESC) (5) (Figure 1). It is impossible to alter the dose of tolvaptan during the first 48 h of this study unless an adverse event was observed. After this period, the attending physicians decide whether to continue tolvaptan therapy. The standard treatments for heart failure, including the angiotensin-converting enzyme inhibitors, angiotensin II receptor blockers, vasodilators, beta-blockers, or digoxin, as well as the change from intravenous to oral loop diuretic or loop diuretic withdrawal, are left to the attending physicians 48 h after admission.

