#### Statistical Methodology

The intention-to-treat the population, which included all randomized patients to whom at least one dose of tolvaptan was administered, will be analyzed for the primary and secondary endpoints. As an exploratory analysis, we will evaluate interactions between tolvaptan add-on treatment and pre-specified subgroups on primary and secondary outcomes. Subgroups were defined for age (age > 65 and ≤ 65), eGFR at admission (eGFR 15–29 and eGFR 30–60), sodium and chloride levels at admission (above or below median), furosemide-naive or not, diuretic response achieved in the first 2 h after initial intravenous injection, blood urea nitrogen/creatinine (above or below median), and left ventricular ejection fraction ≤ 40 or >40%. A *P*-value of < 0.05 was considered statistically significant. Continuous variables are expressed as mean ± standard deviation if normally distributed or as median (interquartile range) if otherwise. When necessary, the variables were transformed for further analysis. Statistical significance was defined as two-sided 5%, and all analyses were performed using IBM SPSS^®^ (version 24.0) and R version 3.5.2 (R Foundation for Statistical Computing, Vienna, Austria; ISBN 3-900051-07-0, URL http://www.R-project.org). Normality was assessed using the Shapiro-Wilk test. The independent Student's *t*-test or Mann-Whitney U test was used to compare the two treatment groups according to each parameter. Categorical data will be displayed as a percentage or number and compared using Fisher's exact test. The relationship between baseline characteristics and outcomes will be compared by one-way analysis of variance, Kruskal-Wallis test, or χ^2^ test, as appropriate.

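### Free improvement: compare furosemide dose on the log scale, adjusted for the dose given before randomization, because the stated unadjusted test of a raw total can lose precision

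*Protocol article*

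**What the plan says.** - **Endpoint.** The abstract counts the furosemide total among the key secondary endpoints: "The key secondary endpoints include the improvement of fractional excretion of sodium at 6 h, the total dose of furosemide". The Endpoints section lists it without ranking: "improvement of fractional excretion of sodium at 6 h, total dose of furosemide, changes in the body weight, net fluid loss". Neither place relates it to the patient's starting or home dose.
- **Starting dose.** Under Study Flow and Loop Diuretic Strategy, patients already on a loop diuretic receive "a starting dose of intravenous furosemide that is one to two times the 24-h oral furosemide dose prescribed before the admission home dose". The others receive "20–40 mg for treatment-naive patients with loop diuretic".
- **Timing.** Eligible patients are allocated afterwards: "at 2 h after the first intravenous furosemide, they will be randomly assigned 1:1". The first dose is therefore a pre-randomization characteristic.
- **Later dosing.** The definition of clinically relevant worsening renal function mentions a creatinine rise "accompanied by the doubling of furosemide dose according to the diuretic treatment protocol". The full algorithm is in Figure 1, which is not shown.
- **Test.** Statistical Methodology offers the independent t-test as one option and for the other says "Mann-Whitney U test was used to compare the two treatment groups according to each parameter". Transformation is allowed when necessary. Prior furosemide use appears only as an exploratory subgroup, and the Randomization section states no stratification.

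**The concern.** Tolvaptan can change only the furosemide given after allocation. If later doses are built on the first one, a patient with a high home dose will have a high total in either arm, and the two-group test treats that spread as noise. For example, the starting rule gives an untreated patient as little as 20 mg and a patient with an 80 mg home dose 80–160 mg, a 4- to 8-fold difference before allocation.

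The Introduction credits tolvaptan with reducing the loop diuretic dose, and this endpoint tests that. A moderate saving could be missed although a known, recorded baseline variable would explain much of the noise.

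**Working it through.** **1. The plan's own sample size.** Inputs from the Sample Size section: difference 1,000 ml, SD 1,595 ml, 90% power, 15% dropout; two-sided 5% from Statistical Methodology. Per arm, n = 2 × (1.960 + 1.282)² × (1,595/1,000)² = 53.5, so 54 per arm and 108 in all. 108/0.85 = 127.1, or 128 as an even number. The stated figure reproduces. It is sized on urine output; nothing is stated for furosemide dose.

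**2. What that size gives any continuous endpoint.** With 54 per arm, the unadjusted test detects (1.960 + 0.842) × √(2/54) = 0.54 SD at 80% power, or 0.62 SD at 90%.

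**3. Cost of leaving out a baseline covariate.** If the adjusted analysis has 90% power, the unadjusted one has Φ(3.242 × √(1 − R²) − 1.960), where R² is the share of variance that the covariate explains: 83% at R² = 0.2, 71% at 0.4, 54% at 0.6 and 30% at 0.8.

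**4. How it depends on the dosing algorithm.** Let log later dose = constant + e × log starting dose + noise. With e = 1, later doses are proportional to the first; with e = 0, they are unrelated to it. Assumed, not from the documents: SD of log starting dose 0.72, noise SD 0.4, a true 25% reduction (ln 0.75 = −0.288) and 55 per arm (√(2/55) = 0.1907). Power = Φ(0.288/(SD × 0.1907) − 1.96), with SD equal to:
- unadjusted log later dose: √(e² × 0.72² + 0.4²)
- log ratio of later to starting dose: √((1 − e)² × 0.72² + 0.4²)
- ANCOVA on log starting dose: 0.4 for every e

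| e | Unadjusted: SD, power | Ratio: SD, power | ANCOVA: power |
|---|---|---|---|
| 1 | 0.824, 45% | 0.400, 96% | 96% |
| 0.5 | 0.538, 80% | 0.538, 80% | 96% |
| 0.25 | 0.439, 93% | 0.672, 61% | 96% |
| 0 | 0.400, 96% | 0.824, 45% | 96% |

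The ratio beats the unadjusted later dose only when e exceeds 0.5. ANCOVA is never worse than either.

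**5. Simulation of the raw total.** This total includes the first dose, which tolvaptan cannot change. Same effect and size; 30–50% of patients furosemide-naive; home doses 20/40/80/160 mg with probabilities 0.3/0.4/0.2/0.1; median later dose five times the starting dose; no cap or an 800 mg cap over 48 h. With e = 1, power is 20–23% (raw t), 31–38% (Mann-Whitney) and 94–96% (log ratio). With e = 0, the raw t-test reaches up to 88% and Mann-Whitney up to 90%. With weak or no tracking (e = 0.25 or 0), the ratio has only 41–63%. Log-scale ANCOVA holds at 94–97% throughout. A tighter assumed cap of 400 mg lowers ANCOVA to 87% at worst, with Mann-Whitney at about 29% in that setting.

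**6. Other dose mixes.** Total proportional to starting dose, 54 per arm, from a narrow mix (70% naive, home doses 20–40 mg) to a wide one (20% naive, 20–160 mg):

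| True reduction | Raw t | Mann-Whitney | Log ANCOVA |
|---|---|---|---|
| 20% | 19–52% | 23–60% | 82–83% |
| 30% | 45–89% | 50–95% | over 99% |
| 40% | 75–99% | 80–100% | 100% |

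With no true effect, every method rejects in about 5% of runs. A log transformation alone does not help much: in the middle mix (50% naive) at a 30% reduction, a t-test on log totals has 70% power, Mann-Whitney 71%, log ANCOVA over 99%.

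**The case against.** **The premise is only partly visible.** That later doses build on the first is inferred from one clause in a secondary definition; the algorithm is in a figure that is not shown. If doses converge to common levels, the stated tests do well. This stands, and it is why the power range is so wide.

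**It is not an error.** The starting dose precedes allocation, so it is balanced in expectation. A chance imbalance can occur: with log-SD 0.72 and 55 per arm, the 95% range for the ratio of geometric mean starting doses is exp(±1.96 × 0.72 × 0.1907), or 0.76 to 1.31. The p-value already allows for that. This stands too.

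**Covariates are often left to an analysis plan, and Appendix 3 is not shown.** Silence on whether the first dose counts in the total is therefore not held against the article. The article does, however, name an unadjusted test for each parameter, and that choice can be improved on. The transformation clause deals with skew and the naive-or-not subgroup with effect modification; neither removes the variance due to starting dose.

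**Stronger readings.** A reader might infer that home-dose variation swamps any tolvaptan effect. The documents do not support this: they give no home-dose spread, naive share, SD of total dose or expected saving, and in the mixes tried a 40% reduction is still found with 75–99% power by the raw t-test. A reader might also infer that dividing by the starting dose is equivalent to adjusting for it. It is not, unless later doses are proportional to the first. Nor is this one of only three key secondary endpoints: the abstract's list of three is introduced as not exhaustive.

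**Conclusion.** The point holds as a free improvement. The stated comparison is valid and unbiased, but inefficient to the extent that later furosemide doses follow the starting dose. For a 25% reduction with 55 per arm, power is about 20–88% (raw t) or 31–90% (Mann-Whitney), against about 94–97% for log-scale ANCOVA on the pre-randomization dose.

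The low ends apply if later doses are proportional to the first, the high ends if they are unrelated. Part of the gain comes from leaving out the first dose and using the log scale, not from the covariate alone. All these figures rest on assumed dose mixes, an escalation log-SD of 0.4 and no cap or a loose one. In every setting tried, adjustment did at least as well as the stated tests. The primary endpoint, the sample size of 128 and the treatment rules are not touched.

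**What to change.** Define the analysed quantity as cumulative furosemide from randomization to 48 h. Compare arms by ANCOVA on its logarithm, with treatment and the logarithm of the pre-randomization intravenous dose as terms, and report the adjusted ratio of geometric means with its confidence interval. Keep the raw total in mg as a descriptive summary by arm.

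Do not make the ratio of later to starting dose the endpoint. If a patient can receive no furosemide after randomization, state in advance how a zero is handled on the log scale.

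The cost is a change of wording in the endpoint and the analysis. The first dose is set by the protocol and given to every patient, so no new data, patients or treatment changes are needed. The result becomes a ratio, which is less familiar than mg; the descriptive summary covers that.

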**Exclusion criteria**
1. Acute coronary syndrome 2. Anuria in the first 2 h after admission 3. Sepsis 4. Consciousness impairment 5. Pregnant or breastfeeding women 6. Severe valvular heart diseases (severe valvular stenosis or regurgitation) 7. Admission sodium level >140 mEq/L 8. Serum total bilirubin > 3mg/dL 9. Serum potassium >5.5 mmol/L 10. Allergy or contraindication to tolvaptan 11. Emergency indication for hemodialysis 12. Cardiogenic shock or mechanical circulation support

* *The wet-warm phenotype is defined as a patient with ≥2 clinical signs of congestion (bibasilar rales, bilateral ankle edema, ascites, jugular venous distension) and N-terminal pro B-type natriuretic peptide (NT-proBNP) at admission ≥900 pg/ml*.

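### The 48-hour NT-proBNP change has no stated scale and only an unadjusted comparison; a log-ratio analysis should be fixed in advance, because a pg/ml change would cost power

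*Protocol article*

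**What the plan says.** - **Endpoint.** The Endpoints section names "incidence of clinically relevant WRF, and changes of NT-proBNP at 48 h" at the end of its list of secondary endpoints. It does not define the scale of the change. It refers to Appendix 3 for a summary, which is not shown. The Abstract does not count NT-proBNP among the key secondary endpoints.
- **Sampling.** The Measurements section says that NT-proBNP, with the liver enzymes, "were evaluated upon admission and at the end of the study". I take the second sample to be the 48-hour one.
- **Entry.** The footnote to Table 1 requires "N-terminal pro B-type natriuretic peptide (NT-proBNP) at admission ≥900 pg/ml". No upper limit is stated.
- **Analysis.** The Statistical Methodology section says "Normality was assessed using the Shapiro-Wilk test" and then "The independent Student's *t*-test or Mann-Whitney U test was used to compare the two treatment groups according to each parameter". No model with the admission value is named for any between-arm comparison.
- **Transformation.** The same section adds "When necessary, the variables were transformed for further analysis". It names no variable and no transform, and does not say whether the transform is applied before or after the change is taken.

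**The concern.** A change in pg/ml scales with the starting value. A 30% fall is 300 pg/ml from 1,000 and 9,000 pg/ml from 30,000. If treatment acts proportionally, a pg/ml change mixes the patient's response with the patient's admission level, and the admission level is noise for the comparison of arms. The difference of logs removes it.

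The transformation sentence does not settle the matter. A pg/ml change can be negative or positive, so it cannot be logged once taken; the log has to come first, and nothing says so. The sentence also lets the scale be chosen after the data are seen, in an open-label trial.

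What is at stake is power, and a scale fixed in advance, for one secondary endpoint. NT-proBNP is read in the laboratory, whereas dyspnea is scored on a Likert scale and the Discussion concedes that behaviour can change in an open-label design.

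**Working it through.** **1. The plan's own figure.** The Sample Size section gives a difference of 1,000 ml, SD 1,595 ml, 90% power, a 0.05 type I error (two-sided per Statistical Methodology) and 15% dropout.

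n per arm = 2 × (1.960 + 1.282)² × 1,595² / 1,000² = 2 × 10.51 × 2.544 = 53.5, so 54. Inflated: 54 / 0.85 = 63.5, so 64 per arm and 128 in total. The stated 128 is reproduced. It rests on urine output alone, so I use 54 evaluable patients per arm for NT-proBNP.

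**2. Assumed inputs, none from the documents.** Median admission value 5,000 pg/ml; ln-SD of admission values 0.8-1.2; control 48-h/admission ratio 0.75; a further 25% proportional fall on tolvaptan (between-arm ratio 0.75); ln-ratio SD 0.4-0.5.

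**3. Log ratio, by hand.** Effect = ln 0.75 = -0.288. Standard error = SD × √(2/54) = SD × 0.1925.
- SD 0.5: 0.288 / 0.0962 = 2.99; power ≈ Φ(2.99 - 1.96) = Φ(1.03) = 85%.
- SD 0.4: 0.288 / 0.0770 = 3.74; power ≈ Φ(1.78) = 96%.

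Simulation gives 83-97%, in agreement. Under this model the log-ratio power does not depend on the spread of admission values.

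**4. pg/ml change, by simulation, same inputs (ranges over repeated runs).**
- Shapiro-Wilk rejects normality of the change in more than 99% of trials, so the plan's rule leads to Mann-Whitney.
- Mann-Whitney on pg/ml change: about 55-78%.
- At ln-SD 1.0 and ratio SD 0.5: Mann-Whitney 59%, log ratio 83%, a loss of 24 points.
- The t-test on pg/ml change, which the rule would almost never select, has 27-61%.

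**5. A second model.** Here log values at admission and 48 h correlate 0.7-0.9, admission values are cut at 900 pg/ml, and there are 2,000 runs per setting.
- Log-SD 1.0, correlation 0.8, between-arm ratio 0.7: Mann-Whitney on pg/ml change 47%, t-test on log change 83%, log model with the admission covariate 87%.
- Between-arm ratio 0.8, over log-SD 0.8-1.2 and all correlations: 15-51%, 24-90% and 26-91% respectively.
- The covariate adds about 0-5 points, so nearly all the gain comes from the log scale.
- No treatment effect (log-SD 1.0): rejection rates are 4.4-5.6% across all methods. With 2,000 runs the simulation error is √(0.05 × 0.95 / 2,000) = 0.5 points, so every method is valid when fixed in advance.

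**The case against.** **The pg/ml scale is not in the plan.** This is correct. If the change means percentage change, Mann-Whitney ranks patients by the 48-h/admission ratio and loses almost nothing: 82-96% against 85-97% for the log-ratio t-test under the same assumptions. The power loss is therefore conditional on a pg/ml reading.

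**The transformation sentence already permits the remedy.** It permits it: logging first and then taking the change gives the log ratio. But it does not commit to it. Under the assumed effect, Mann-Whitney on pg/ml change and a t-test on the log ratio disagreed on significance in 19-31% of simulated trials, so the choice can decide the result.

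**An article leaves such detail to an analysis plan.** That is largely fair, and Appendix 3 or a fuller plan may define the scale. The point survives because the article does state a method, an unadjusted test for each parameter with an open option to transform, and a better one is available at no cost.

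**The log scale does not guarantee adequate power.** True. With a 15% relative effect, ln 0.85 = -0.163; dividing by 0.0962 and 0.0770 gives 1.69 and 2.11, so power is about 39-56%.

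**Stronger readings that a reader might infer.**
- *Extreme admission values dominate the result or set its sign.* In the second model the fifth of patients with the highest admission values supply about 70-85% of the variance of the pg/ml change, but this matters for the t-test, a branch that the plan's rule would hardly ever take.
- *Ranks of the pg/ml change mainly follow admission level.* Under the assumptions of step 2 their Spearman correlation is 0.69-0.79 with the patient's ratio and 0.44-0.57 (absolute) with admission value. The ranks follow response more than starting level.
- *A real fall is likely to be missed.* Mann-Whitney power of 55-78% under the assumptions of step 2 does not support that.

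**Conclusion.** The concern holds in a limited form. The article fixes neither the scale of the NT-proBNP change nor an adjustment for the admission value, and leaves transformation to later judgement. If the change were taken in pg/ml, the plan's rule would lead to Mann-Whitney with about 55-78% power, where the log ratio has 83-97%.

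These figures rest on a right-skewed marker, a proportional treatment effect and the spreads assumed above, none of which the documents give. The direction was the same in every scenario with a treatment effect; the size was not. The loss is one of power, not validity, and it falls on a secondary endpoint that is neither key nor used for sizing. The primary endpoint and N = 128 stand.

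**What to change.** State in the analysis plan, before any comparison by arm, that the endpoint is log(48-h/admission NT-proBNP), analysed in a linear model with treatment and log admission NT-proBNP. Report the between-arm geometric mean ratio with 95% CI. With the log admission value in the model, using the log 48-hour value as the response gives the same treatment estimate, so either form will do. Changes in pg/ml can still be described but should not be the tested quantity.

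The cost is one sentence. The samples and the sample size stay as they are; the only change for readers is a ratio in place of a difference in pg/ml. If Appendix 3 or a fuller plan already fixes this scale, citing it is enough.

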**Inclusion criteria**
1. Aged 20–75 years 2. Admitted to hospital with a primary diagnosis of acute heart failure with wet-warm phenotype^*^ 3. Cumulative urine volume output <300 mL within 2 h after the first dose of intravenous furosemide 4. eGFR at admission 15–60 mL/min/1.73 m^2^

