**Figure 1 F1:**
[figure not shown]
Study protocol. At 24 h, study participants will be evaluated by the same investigator ([name], [name], [name], [name], or [name] ). If the investigator determines that the patient is absolutely hypovolemic and symptomatic, the study protocol will be ended.

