### Statistical Consideration

#### Sample Size

In the REALITY-AHF dataset (*n* = 1682) (15), we identified and retrieved the records of the patients treated with an intravenous furosemide within 30 min of emergency department visits. Using the ESC Heart Failure Association definition (<150 ml urine output/h), we identified 95 patients with diuretic resistance in the first 90 min, while their urine output within 48 h was 3,896 ± 1,595 ml. Assuming that the add-on tolvaptan therapy could yield 1,000 ml more urine output at 48 h, we calculated the sample size of 128 patients with an enrollment ratio of 1:1 after adjusting for 15% dropout during the follow-up period. This sample size was intended to provide a 90% power and 0.05 type I error probability.

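### The renal endpoint has no dialysis component, so a patient who starts dialysis before meeting both parts of the definition is scored as having no worsening renal function

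*Protocol article*

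**What the plan says.** The abstract of the protocol article (Methods and Results) names "the incidence of worsening renal function (WRF) at 48 h" among the key secondary endpoints. The Endpoints section gives the operational rule: "Clinically relevant WRF is defined as an increase in serum creatinine level ≥0.3 mg/dl within 48 h accompanied by the doubling of furosemide dose", where the doubling is the one prescribed by the diuretic treatment protocol. I take these to be the same endpoint.

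The Measurements section fixes the sampling: "After randomization, serum urea and creatinine will be re-assessed at 24 and 48 h". The Statistical Methodology section gives the comparison: "Categorical data will be displayed as a percentage or number and compared using Fisher's exact test".

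For the patients themselves, dialysis appears only among the exclusion criteria in Table 1: "Emergency indication for hemodialysis". It is not in any endpoint listed in the article. The safety topics of special interest cover sodium, potassium and liver enzymes, with no renal item. The inclusion criteria admit patients with "eGFR at admission 15–60 mL/min/1.73 m" (per m², squared) and a poor urine response to the first intravenous furosemide dose.

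**The concern.** The two parts of the definition are joined by *and*, and starting dialysis can defeat each of them. Dialysis removes creatinine, so a sample taken afterwards may not show the required rise. It may also replace further diuretic escalation, so the doubling may never happen. The patient with the most severe renal outcome then fails the definition and is scored with the patients whose kidneys did well.

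This matters because renal harm is part of the trial's question. The abstract's conclusions and the Discussion name severe WRF, together with electrolyte disturbance, as risks that could outweigh the benefit of combining diuretics. If dialysis is started more often in one arm, that arm's WRF rate is understated by more, and the comparison is biased in its favour. The documents give no reason to expect one direction over the other.

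**Working it through.** **1. The plan's own figure.** The only sample size stated is for 48 h urine output. Inputs from the Sample Size section: SD 1,595 ml ("their urine output within 48 h was 3,896 ± 1,595 ml"), difference 1,000 ml, power 90%, type I error 0.05, dropout 15%, ratio 1:1. Statistical Methodology makes the test two-sided.

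- n per arm = 2 × (1.960 + 1.282)² × 1,595² / 1,000² = 53.5, rounded up to 54
- With dropout: 54 / 0.85 = 63.5, rounded up to 64 per arm, 128 in total

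The stated 128 is reproduced. WRF plays no part in it, so changing the WRF definition leaves it alone.

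**2. How the stated rule scores each course within 48 h.**

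| Course after randomization | Creatinine part | Furosemide part | Scored as |
|---|---|---|---|
| Both parts met, no dialysis | met | met | WRF |
| Both parts met, then dialysis or death | met | met | WRF |
| Dialysis before a qualifying creatinine value | may never be seen | may not occur | no WRF if either is missing |
| Creatinine rise seen, dialysis instead of doubling | met | not met | no WRF |
| Death before any post-randomization creatinine | no value | either | not stated |

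Rows 3 and 4 are the defect. Row 2 is handled properly. Row 5 is a matter of missing data on which the article is silent.

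**3. Size per patient.** With 64 analysed per arm, one missed patient changes that arm's rate by 1/64 = 1.6 percentage points. If only the 54 assumed to remain after dropout are analysed, it is 1/54 = 1.9 points.

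**4. Illustration with assumed counts.** The documents give no WRF or dialysis rate, so every count below is an assumption. Take 64 per arm and let k patients in arm A start dialysis without meeting both parts. Differences are A minus B in percentage points, with Fisher's exact p in brackets.

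| Recorded WRF, A v B | k | As worded | If k are counted as events |
|---|---|---|---|
| 10 v 16 | 1 | −9.4 (0.27) | −7.8 (0.39) |
| 10 v 16 | 4 | −9.4 (0.27) | −3.1 (0.84) |
| 6 v 13 | 1 | −10.9 (0.13) | −9.4 (0.22) |
| 6 v 13 | 4 | −10.9 (0.13) | −4.7 (0.65) |
| 16 v 16 | 1 | 0.0 (1.00) | +1.6 (1.00) |
| 16 v 16 | 4 | 0.0 (1.00) | +6.25 (0.56) |

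For the first and fourth entries: 10/64 − 16/64 = −9.4 points, and (10 + 1)/64 − 16/64 = −7.8 points; (6 + 4)/64 − 13/64 = −4.7 points. The rule as worded gives the same answer whatever k is. No p-value in the table falls below 0.05 under either scoring, so what moves is the estimated difference, not a finding of significance.

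**The case against.** **The article is condensed.** Appendix 3, which summarises the endpoints, and any SAP are not shown, and handling of deaths and missing values commonly belongs there. This stands for deaths and missing samples. It does not stand for dialysis: what counts as an event is protocol content, the article states a complete rule, and that rule gives a poor answer for a foreseeable course.

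**A patient may qualify before dialysis.** The definition says within 48 h and does not bar an unscheduled creatinine taken before dialysis. How far creatinine falls also depends on the timing and amount of dialysis. Both points stand. The concern is therefore limited to patients who start dialysis before meeting both parts.

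**Dialysis would appear among adverse effects, which are compared by arm.** Probably so, and the information would not be lost to the trial. The WRF comparison would still be wrong.

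**Such patients may be rare.** The exclusions for an emergency dialysis indication, anuria, sepsis, shock and high potassium make early dialysis less likely. This stands, and no rate can be read from the documents. The Discussion reports renal failure of 15% and 18% in the arms of an ultrafiltration trial, but that trial studied other patients and the article gives no 48 h figure for it. The 15% dropout allowance is not a dialysis rate either. A reader might assume rates and quote a share of events missed. With 1 to 3 missed patients against 6 to 13 recorded events, that share runs from 1/13 = 8% to 3/6 = 50%, which reflects only the assumption.

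**Adding procedures or deaths to a renal endpoint brings its own problems.** This stands in part. Death is not in itself renal worsening. The Discussion describes ultrafiltration as an alternative to stepped diuretics, so its use need not mean renal failure. In an open-label trial, starting dialysis is partly the clinician's decision.

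**Conclusion.** The concern holds in limited form. The definition requires a creatinine rise and a furosemide doubling together, so a patient who starts dialysis for renal failure before meeting both is scored as free of WRF in a key secondary endpoint. Each such patient understates that arm's rate by about 1.6 points, on the assumption of 64 analysed per arm. How many there will be is unknown, and the bias could favour either arm.

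A reader might infer that everyone who is dialysed or dies within 48 h is counted as having no worsening or is dropped from the comparison. The documents do not support that. Those who qualify first are counted, and the article does not say how a patient without a creatinine value is handled. The primary endpoint, its analysis and the total of 128 are untouched.

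**What to change.** In the Endpoints section, keep the current definition of clinically relevant WRF and add an alternative event: *or start of renal replacement therapy for renal failure within 48 h*. Wording it by indication keeps out ultrafiltration used only to relieve congestion. Report by arm how many patients qualify through creatinine with furosemide doubling and how many through renal replacement therapy. Report deaths before 48 h by arm alongside the endpoint, not as WRF events.

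The cost is one sentence and one extra table row or two. Start of dialysis should already be in the hospital record. The event rate may rise slightly. The added component is open to clinician judgement in an open-label trial, which is why the components should be shown separately. The change concerns scoring only and alters no patient's care.
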